## 12.4 Identification of AEs

In this study population (S)AEs are expected due to the participants being older residents in a care home setting. Care home staff are responsible for recording AEs for their residents, in the care home records as per standard practice. It is anticipated that most AEs related to infection and falls will be captured as part of the study CRF, but other AEs will not be recorded in the study documentation unless required for outcome measures.

## 12.5 Operational definitions for (S)AEs due to residents health status

Expected SAEs relating to residents' health status include (but are not limited to);

- Infection complications such as pneumonia
- Falls and near falls using PROFANE (Prevention of Falls Network Europe consensus, see <http://www.propane.eu.org/>) definitions respectively for falls as "an unexpected event in which the participants come to rest on the ground, floor, or lower level"
- Frailty syndromes such as delirium and constipation
- Prolonged hospitalisation due to complications from initial injury
- Prolonged hospitalisation due to social care needs
- Pressure sores due to immobility

Death is also an expected outcome in this population.

SAEs related to the health status of older people will **not be** recorded or reported in this study (unless collected as one of the outcomes measures). This study is classified as low risk (the risk to participants taking part is no higher than that of standard care).

## 12.6 Operational definition of SAEs related to research procedures

We do not expect there to be any SAEs related to a research procedure, except for an SAE possibly related to the intervention. The only expected SAE related to the intervention (use of an air filter) is a trip, fall or injury due to the air filtration unit being placed in a resident's bedroom or in a communal area. SAEs that are related and expected will be recorded on the SAE log.

If an SAE occurs that care home staff judge to be related to a research procedure and is unexpected, this will be recorded on the SAE log and reported to the sponsor on a sponsor approved SAE form with 24 hours of becoming aware of the event.

Reportable SAEs include those relating to care home staff, residents or visitors.

## 12.7 Recording and reporting SAEs related to the research procedure

All SAEs that are related to the research procedure/ intervention and unexpected must be reported on a sponsor approved SAE initial report form, this may be provided orally but a written *SAE/SAR Initial Report Form*

must be completed within 24 hours of staff becoming aware of the event. A record of all recordable SAEs must be kept in the site file.

SAEs that are assessed as being possibly, probably or definitely related to the intervention/research procedure and unexpected, from baseline data collection until completion of the last trial-related procedure will be subject to expedited reporting procedures.

For all reportable SAEs the following information (as a minimum) will be collected:

- Full details in medical terms and case description
- Event duration (start and end dates, if applicable)
- Action taken
- Outcome
- Expectedness criteria
- Seriousness criteria

Sites should scan and email the SAE form, with high importance, to the (i) Sponsor, (ii) AFRI-c central trial team (Trial Manager), and (iii) cc'd [name], Chief Investigator; see 'Key Trial Contacts' for contact details (pages 2-3).

(Please note: typical University (central trial team) staff working hours are Monday to Friday, 09:00-17:00 (subject to variation). In the event of University closure dates or limited availability, an out of office automatic response will notify the site of alternative contact details/arrangements).

The Sponsor and/or central trial team will confirm receipt and, if required, forward the completed form to REC within the reporting periods (see below).

Each SAE must be reported to the Sponsor separately and not combined on one SAE form. Any change of condition or other follow-up information relating to a previously reported SAE should be documented on the separate *SAE/SAR Follow Up Report Form* provided by the central trial team.

Events will be followed up until the event has resolved or a final outcome has been reached.

**Figure 4 Overview of safety reporting requirements for SAEs related to the research procedure/intervention**

[figure not shown]

## **12.8 Responsibilities related to SAE reporting**

**Study champions** – Study champions (or suitably trained delegates, including delivery teams) at each site be responsible for recording/reporting any SAEs that are related to research procedures this will include

- Using their professional judgement in assessing and assigning seriousness, causality and expectedness (where needed, the central study team will support this assessment).
- Ensuring that all appropriate S/AEs are documented.
- Ensuring that all SAEs are recorded and reported as per the procedures noted above, including the provision of further follow-up information as soon as available.
- Ensuring that SAEs are chased with the Sponsor/central trial team if a record of receipt is not received within 2-working days of initial reporting.

Study champions should also comply with any internal SAE reporting requirements within their care home.

**Chief Investigator (CI)** – The CI (or agreed delegate) will be responsible for:

- Clinical oversight of the safety of residents participating in the trial, including an ongoing review of the risk/benefit.
- Using medical judgement in assessing and assigning seriousness, causality and expectedness of SAEs where it has not been possible to obtain local medical assessment.
- Immediate review of SAEs requiring expedited reporting.
- Ensuring safety reports are prepared in collaboration with appropriate members of the TMG group for the relevant oversight committees and regulatory authorities.
- Expedited reporting of SAEs to the REC within required timelines.
- Notifying PIs of SAEs that occur within the trial.
- Central data collection of SAEs.

**Trial Manager** – The Trial Manager will provide a summary of S/AEs to the TSC and Sponsor as required.

## **12.9 Safeguarding procedures**

Should residents or staff disclose information to suggest that they or others are at significant risk of harm, we may need to disclose these details to the designated safeguarding authority. A safeguarding protocol for researchers and participants will be implemented. See section 8.5 for details of the safeguarding procedure for residents during interviews.

## 13 STATISTICS AND HEALTH ECONOMICS ANALYSIS

### 13.1 Main trial

#### 13.1.1 Sample size calculation

Previous research suggests ~30% of residents will wish to take part and ~40% will leave the care home or die during the study,(34) reflecting the frailty and vulnerability of the study population. To maintain study power, we will continually recruit new residents, resulting in an expected overall study data attrition of ~20%. We consider the advantages in power outweighs the potential disadvantage arising from the unblinded recruitment of a proportion of study participants.

Data are surprisingly limited(45) regarding the incidence of infections in care homes. One widely cited study suggests healthy adults experience four to six respiratory per year.(46) A recent study found UK care home residents experienced an average of one respiratory infection per annum.(34) Other studies suggest the incidence of all medically diagnosed infections range from 3 to 9.8 per 1,000 resident care days, equivalent to between 1 and 3 infections per resident per year.(45) (5) Another study suggested the incidence of all infections per resident is one to three infections per annum,(47) with around 50% considered to be respiratory.(48)

Considering these together, and based on PPI and investigator experience, we expect care home residents to experience two respiratory infections during the winter months (usually 1 Sept to 31 May = 273 days). This will be monitored closely as one of our stop/go criteria (Table 2). Our PPI group advised that a reduction of one infection would be important to residents, relatives and staff.

Based on 90% power and an alpha of 0.05, to detect a reduction in winter respiratory infections of 1 per 242 person days from 2 to 1 per 242 person days, assuming a coefficient of variation of 0.78 to allow for between care home infection rate variation, calculated from data provided in personal communication from the PRINCESS study team,(34) a total of 74 care homes will be required. This assumes a mean cluster size of 12 for winter 3 (10 participants per care home for winters 1 & 2) and accounting for an attrition level as observed in PRINCESS,(34) and the continual recruitment strategy as described above, each cluster will provide a mean of 1920 person days of follow up. After reviewing accumulating data with the DMC and TSC on the number of follow up days, a decision was made to increase the number of care homes taking part in Winter 3 from 32 to 46 in order to achieve the number of person days required in the original calculation. This gives an approximate total of 91 care homes taking part in the study overall.

Each care home will participate for a single winter season (usually 1 Sept to 31 May). We estimate that 10 care homes will be randomised in winter 1 (the most experienced) and then 35 in winter 2 and 46 in Winter 3.

#### 13.1.2 Data and statistical analysis

Analyses and reporting will be according to CONSORT guidelines(49) and will be pre-specified prior to the analysis in a detailed statistical analysis plan. Baseline data will be presented by trial arm, for both individual- and cluster-level characteristics, using descriptive statistics. Continuous measures will be presented using a measure of central tendency and variation as appropriate and categorical data as frequencies and percentages.

The primary effectiveness analysis will be conducted on the "consented" under the intention to treat principle (ITT) using mixed effects Poisson regression to estimate an incidence rate ratio (along with associated 95% confidence interval and p-value), comparing incidence of resident winter respiratory infection between groups. The primary analysis model will adjust for nursing care provision and deprivation tertile (stratification variables) and will include a random effect for care home to account for clustering. The use of a mixture distribution that captures the variation in rates across care-homes, and/or zero inflated models will be explored dependent on the nature of the data obtained. Robust standard errors will account for clustering if mixed effects models fail to converge.

The effect of the intervention on secondary outcomes in the "consented" will be investigated using the same analytical approach as in the primary analysis; using mixed effects regression models that are appropriate to the nature of the outcome being analysed (e.g. a logistic model for a binary outcome). Analyses will be repeated using anonymous data collected on all residents.

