| Aim                  | The overall aim is to investigate the clinical and cost effectiveness of portable HEPA air filters in reducing symptomatic winter respiratory infections (including COVID-19) in residents of older people's care homes.                                                                                                                                                                                                                                                                                                                                                                                                                                                                                                                                                                                                                                                                                                                                                                                                                                                                                                                                                                                                   |
| Trial design         | A two-arm, open controlled trial with 1:1 cluster randomisation to intervention or control at care home level, stratified by nursing care provision and socioeconomic status, with nested: mixed-method process evaluation; internal pilot (with go/no-go criteria); and health economic evaluations.                                                                                                                                                                                                                                                                                                                                                                                                                                                                                                                                                                                                                                                                                                                                                                                                                                                                                                                      |

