|                                                                                                                                  | Care home level data collection  |                                                                                  |   |   |   |   |
| Number of days experiencing PCR or other microbiologically confirmed infection outbreaks                                         |                                  |                                                                                  |   |   |   | ● |

a Expected time periods for winters 2 and 3. Internal pilot timing will differ.

b Period within which intervention care homes are requested to turn on air filters, and both intervention and control group care homes will collect daily symptom data.

c Allowing time for medical records to be updated with letters from other providers. For winters 1 & 2 this period of data collection may occur later.

d See serious adverse event section 12

e To be determined at data analysis where the start/ end definition will be as per previous studies: (30) (31) (32) the onset of two new (or worsening of pre-existing) respiratory symptoms for ≥1 day or one respiratory symptom for ≥2 days; the end the last symptomatic day preceding two asymptomatic days

f To inform primary outcome sensitivity analyses and take account that infections in older people may present non-specifically (33)

g Temperature ≥37.8°C

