#### **6.4.5 Randomisation and allocation specific training**

Following green light activation, and baseline data being received, the care homes will be randomised to receive either the intervention (usual care plus HEPA filters) or control (usual care) (see section 10 and 11). Randomisation will be stratified by whether they provide nursing care yes/no; and socioeconomic tertile (high/medium/low)) using a randomisation list pre-generated by a CTU statistician with no other involvement in recruitment activities.

Following randomisation, care homes will be informed of their allocation.

Intervention care homes will complete additional study training, specific to the use of devices in their care homes – e.g. installation, monitoring and maintaining air filters (according to manufacturer instructions), recording of outcomes and the arrangements for delivery of the air filters to the relevant care homes. For care homes allocated to the intervention, training will also involve discussions of where to locate communal room air filters. Staff will then begin inviting an average of 12 (maximum of 16) residents per care home to participate to receive an air filter in their private bedrooms and/or provide access to their medical records (see section 6.5) and share identifiers with the UKHSA.

In the control care homes staff will begin inviting an average of 12 (maximum of 16) residents per care home to participate provide access to their medical records (see section 6.5) and share identifiers with the UKHSA.

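### Winter of participation is missing from the primary model although each home supplies only one of three winters; adding it would recover a little precision at almost no cost

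*Protocol*

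**What the plan says.** - **Model (13.1.2).** "The primary analysis model will adjust for nursing care provision and deprivation tertile (stratification variables"). It also "will include a random effect for care home to account for clustering". Secondary outcomes follow the same approach, and the analyses are repeated on the anonymous data for all residents.
- **Randomisation (6.4.5).** "Randomisation will be stratified by whether they provide nursing care yes/no; and socioeconomic tertile (high/medium/low"). The list is described as a "randomisation list pre-generated by a CTU statistician with no other involvement in recruitment activities". No block size is given. The Trial Summary and section 6.17 name the same two strata.
- **Winters (13.1.1 and 3.3).** "Each care home will participate for a single winter season (usually 1 Sept to 31 May"). Section 13.1.1 expects 10 homes in winter 1, 35 in winter 2 and 46 in winter 3, which makes 91.
- **Timing of winter 1.** Section 3.2 describes a pilot of up to six months ending on 31 May, against the usual September to May period in section 6.1. Footnote a to Table 3 says "Internal pilot timing will differ".
- **Between-home variation (13.1.1).** The coefficient of variation of 0.78 comes from the data of one earlier care-home trial. The protocol does not say whether any of it is seasonal.

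**The concern.** Because a home contributes a single winter, winter is purely a home-level factor. Respiratory infection rates may well differ from one winter to the next, and winter 1 homes also sample a different part of the season. The protocol itself sets its dates on the condition that COVID-19 is still prevalent, so it allows for changing circulation.

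With winter left out, two things follow. The difference between winters is absorbed by the care-home random effect and widens the confidence interval. And since allocation was not stratified by winter, one arm may hold more homes from a high-incidence winter, which moves the observed IRR in that particular trial. What is at stake is the precision of the primary estimate. The same applies to every secondary model built in the same way.

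**Working it through.** **1. Reproduce the plan's own figure.** Inputs from section 13.1.1: 90% power, alpha 0.05, control rate λ0 = 2/242 and intervention rate λ1 = 1/242 per person-day, k = 0.78, y = 1,920 person-days per home. The Hayes–Bennett formula for unmatched clusters is

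c = 1 + (z_α/2 + z_β)² × [(λ0 + λ1)/y + k²(λ0² + λ1²)] / (λ0 − λ1)².

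This gives 36.94, so 37 per arm and 74 homes in total, as stated. Alpha must be two-sided to obtain this; one-sided gives 30.3 per arm.

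**2. Move to 91 homes.** Section 13.1.1 raised the number of homes to recover the original total of person-days: 74 × 1,920 = 142,080, or 142,080/91 ≈ 1,561 per home. With 45.5 homes per arm and k = 0.78, power is 94.5%. The standard error of the log IRR is

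√[1/(45.5 × 1,561 × λ0) + 1/(45.5 × 1,561 × λ1) + 0.78² × 2/45.5] = √(0.0017 + 0.0034 + 0.0267) ≈ 0.178.

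Between-home variation makes up about 84% of that variance (0.0267/0.0319).

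**3. Add a winter component.** The protocol gives no rates by winter, so the ratios below are assumptions. With weights 10/91, 35/91 and 46/91, the between-winter coefficient of variation CV_w follows from each set of ratios. If winter variation comes on top of 0.78, then k_total = √[(1 + 0.78²)(1 + CV_w²) − 1]. Adjusting for winter brings k back to 0.78, that is 94.5% power and 37.8 homes per arm for 90% power.

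| Assumed rates, winters 1:2:3 | CV_w | k_total | Power without winter | Gain from adjustment | Homes per arm for 90%, without winter |
|---|---|---|---|---|---|
| 1 : 1 : 1.25 | 0.111 | 0.793 | 94.0% | 0.5 points | 38.9 |
| 1 : 1 : 1.5 | 0.200 | 0.820 | 92.6% | 1.9 points | 41.2 |
| 1 : 1 : 2 | 0.332 | 0.886 | 88.9% | 5.6 points | 47.2 |
| 1 : 2 : 3 | 0.283 | 0.858 | 90.6% | 3.9 points | 44.6 |

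If 0.78 already contains the seasonal part, power without winter stays at 94.5% and adjustment raises it to between 95.1% and 98.2% over the same scenarios.

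**4. Chance imbalance.** With 91 homes permuted freely into arms of 46 and 45, the arms' shares of winter 3 homes differ by more than 10 percentage points in about 30% of allocations. The standard deviation of the shift in log IRR is close to CV_w × √(1/46 + 1/45) = CV_w × 0.210. For a ratio of 1.5 that is 0.200 × 0.210 = 0.042. Simulated 95% ranges of the shift, as a factor on the IRR, are:

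- 0.96 to 1.05 for 1 : 1 : 1.25
- 0.93 to 1.09 for 1 : 1 : 1.5
- 0.88 to 1.15 for 1 : 1 : 2
- 0.89 to 1.13 for 1 : 2 : 3

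If the list instead used blocks of four within six equal strata in order of entry (an assumption), a difference above 10 points would occur in only about 5% of allocations.

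**5. Bias and cost.** Counts were simulated for 91 homes at a true IRR of 0.5 (log −0.693), 600 trials per scenario. Negative binomial models with and without winter were fitted, as an approximation to the planned mixed Poisson model.

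| Assumed rates | Mean log IRR, without / with winter | SD of log IRR, without / with winter |
|---|---|---|
| 1 : 1 : 1 | −0.676 / −0.674 | 0.181 / 0.182 |
| 1 : 1 : 1.5 | −0.689 / −0.693 | 0.190 / 0.181 |
| 1 : 1 : 2 | −0.685 / −0.689 | 0.198 / 0.180 |
| 1 : 2 : 3 | −0.688 / −0.690 | 0.196 / 0.188 |

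The means agree with and without winter. When winters do not differ, adjustment costs essentially nothing.

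These calculations give every home the same number of person-days. Winter 1 homes will have had fewer, but they are only 10 of 91.

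**The case against.** The strongest reply has four parts.

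- **SAP territory.** Section 13.1.2 defers detail to a statistical analysis plan, names the stratification variables as a usual minimum, and does not rule out further covariates. The plan is not shown and could add winter without contradiction. This stands in part: the protocol has not stated anything false. It does, however, name a specific covariate set, and winter can be added to that set at once.
- **Validity.** The random effect for care home already absorbs season, and section 13.1.2 allows a mixture distribution for the variation between homes. This stands in full. A reader might infer that the primary estimate is biased by season; neither the documents nor the simulation supports that.
- **Size.** A reader might infer that the trial is underpowered without winter, or that much of the 0.78 is season. The protocol gives neither winter-specific rates nor a seasonal share of 0.78. At its design effect, power without winter falls below 90% only in the two-fold scenario, and only if winter variation comes on top of 0.78. Larger gains can be produced by assuming a weaker effect such as an IRR of 0.70, or 4-fold to 6.7-fold differences between winters. Those inputs appear nowhere in the protocol and would be illustrative only.
- **Blocking.** A blocked list used in order of entry would partly balance the winters. This stands as a possibility, since block size is not stated. It would reduce the chance shift, but an unadjusted model would still carry the winter variance in its standard error.

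**Conclusion.** The point holds as a modest and nearly free gain in precision. Winter is a known home-level factor that the stated primary model leaves out, and allocation was not stratified on it. The power gain of about 0.5 to 6 points and the chance shifts shown depend on assumed winter rate ratios, on equal follow-up per home and, for the shifts, on unrestricted allocation. If the winters turn out alike, nothing is gained and almost nothing is lost. The point does not call the randomisation, the 74-home calculation or the validity of the IRR into question.

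**What to change.** In section 13.1.2, list winter of participation (1, 2 or 3) as a fixed effect next to nursing care provision and deprivation tertile, keeping the care-home random effect. State that the secondary models and the repeat analyses on the anonymous data carry the same term, and put the same line in the SAP. If the primary model can no longer be changed, name the winter-adjusted model as a sensitivity analysis before the unblinded data are reviewed, so that the choice between the two estimates is not made on the results.

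The cost is two degrees of freedom out of 91 homes. The winter of every home is already recorded, so no data need to be collected. Randomisation need not be changed, and it no longer can be: the document history runs to September 2024, after the usual end of the third winter.
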